## Methods: data collection, management and analysis

### Data collection methods {18a}

The study collected demographic and baseline characteristics from medical records and electronic medical records, including age, sex, type of admission, and baseline characteristics such as body weight, body height, patient history, and pharmacological history. The results of PET/CT scans and physical examinations are documented in the electronic medical records and entered by the trial investigator in the electronic Case Report Form (eCRF).

### Plans to promote participant retention and complete follow-up {18b}

The study site will make every reasonable effort to follow the participant for the entire study period. Study site staff members will be responsible for developing and implementing local standard operating procedures to achieve maximal follow-up.

### Data management {19}

The study data are entered online in an internet-based database (RedCap®) and collected from medical records. The study staff members had access to the medical records of the patients. The investigators will be responsible for screening patients, obtaining informed consent, collecting study data, and entering it into the eCRF. The statistician will analyse the study data in cooperation with the principal investigator. The data will be stored for 15 years after completion of the study and then destroyed. To promote data quality, the eCRFs of each participant will be reviewed by another member of the study team as a monitor.

## Statistical methods

### Statistical methods for primary and secondary outcomes {20a}

All data will be described for each arm separately and for the entire group of patients. The appropriate descriptive statistics will be used, i.e., counts and percentages for categorical characteristics and median and interquartile range (IQR) or mean and standard deviation (SD) for continuous characteristics. Depending on the data type, common statistical tests such as Fisher's exact test or chi-square test for comparing categorical variables and nonparametric Mann‒Whitney test or Kruskal‒Wallis test for comparing continuous variables or their parametric alternatives if the assumption of data normality is met will be used for comparison of patient characteristics between arms.

The survival parameters that will be considered are progression-free survival (PFS) and overall survival (OS). PFS is considered the time from the start of radiotherapy to the occurrence of progression or death. OS is considered the time from surgery to death (in relation to GBM). The Kaplan‒Meier method will be used to estimate the probability of survival. Survival comparisons between groups will be made using the log-rank or Gehan-Wilcoxon test. The Cox proportional hazards model will be used to calculate the hazard ratio in univariable and multivariable analyses.

All statistical tests and confidence intervals will be calculated at a significance level of 5%.

### Methods for any additional analyses {20b}

Not applicable. The subgroup and adjusted analyses are not planned.

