### Trial design {8}

The GlioMET study is an investigator-initiated study. This clinical trial is a prospective, monocentric, open-label, nonrandomized clinical study with a parallel assignment initiated in June 2020.

The main aim of the clinical trial is to improve the progression-free survival of patients with GBM and REP via optimizing of diagnostic and treatment procedures. The experimental drug ^11^C-methionine PET/CT will be administered to all patients recruited to this study and compared to the cohort consisting of a historical group of patients collected in the period 2014–2018. The setting is a confirmatory framework against the historical cohort. A schematic overview of the design of the study is presented in Fig. 1.

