Collection of anamnestic data will take place following standard clinical practice. Taking a family history will focus on the familial occurrence of malignancies and genetic syndromes. As part of the personal anamnesis, pre-existing severe diseases will be recorded even at the time of diagnosis; a pharmacological anamnesis and information on allergies will automatically be included. Data will also be collected regarding substance abuse and social and work anamnesis

^b^Physical and laboratory examination

Physical examination + neurological examination + height/weight/vital functions: BSA calculation, blood pressure, pulse, respiratory rate, body temperature;

Performance status: according to ECOG 0–2; Laboratory examination: blood count including differential count, Na, K, Cl, urea, creatinine, glucose, total bilirubin, ALT, AST, ALP, amylase, LD, albumin, total protein, CRP

^c^Scope of operation

Evaluation according to postoperative MR (performed within 72 h after surgery):

Gross Total Resection: complete macroscopic resection

Subtotal Resection: resection of ≥ 90% of the tumor

Partial Resection: resection of < 90% of tumor (biopsy only = exclusion criterion)

^d11^C-MET PET/CT

^11^carbon radiolabelled methionine positron emission tomography/computer tomography

^e^Quality of life questionnaire

These are standardized questionnaires assessing the quality of life of oncology patients, according to the EORTC. Official versions of the questionnaires in Czech are available. These questionnaires can be completed at home. The basic questionnaire (EORTC QLQ-C30 Czech) contains 30 questions with the possibility of answering a degree of four points or a seven-point Likert scale. Part of the quality of life questionnaires is also a module of an additional 20 questions optimized to assess the quality of life of neuro-oncology patients

^f^Magnetic Resonance Imaging and assessment of RANO criteria

^g^Molecular markers

Immunohistochemical labeling of GFAP, Ki-67, IDH1 and ATRX, PDL1 protein expression by immunohistochemistry, mutational status of TERT and IDH2 genes and then IDH1 in immunohistochemically positive patients by Sanger sequencing, methylation status of the MGMT promoter and 1p/19q codeletion

^h^PoF analysis

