Spatial evaluation of recurrence in relation to the area irradiated with a high dose of radiation (patterns of failure, PoF) is performed by a radiotherapist. MR defining progression according to RANO (MRRANO) criteria is used to analyze PoF, specifically T1-weighted sequence with contrast medium administration

Standard image fusion is performed in the radiotherapy planning system: MRRANO is registered to the original planning CT. The fusion is focused on the calf area (preferential choice of Hounsfield HU units in the bone band)

The modification consists of changing the irradiation plan.

Two chemoradiotherapy regimens of concomitant chemoradiotherapy with temozolomide are permissible at the discretion of the attending physician.

Stupp's regimen can be extended to 12 cycles of adjuvant temozolomide due to the unification of the possible length of administration of adjuvant temozolomide itself and thus minimizing the occurrence of bias in the length of adjuvant treatment between younger and older/frail groups in the clinical study.

Since 2005, when temozolomide was registered based on the study with 6 cycles of adjuvant temozolomide, a number of phase 3 studies were conducted, where it was possible to extend this adjuvant period up to 12 cycles. On the other hand, in patients without REP, extension of adjuvant chemotherapy up to 12 cycles is currently not recommended [2].

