## Methods: assignment of interventions: allocation

### Sequence generation {16a}, Concealment mechanism {16b}

The GlioMET study is nonrandomized, and the assignment of interventions is not applicable.

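### The confirmatory PFS comparison with a non-randomised historical cohort has no settled adjusted analysis and no single named test, so a case-mix difference could pass for a PET effect

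*Protocol article*

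**What the plan says.** - **Design.** Trial design {8} has all patients receiving PET "compared to the cohort consisting of a historical group of patients collected in the period 2014–2018" and adds: "The setting is a confirmatory framework against the historical cohort". Under allocation {16a, 16b}: "The GlioMET study is nonrandomized, and the assignment of interventions is not applicable".
- **Primary outcome.** Outcomes {12} makes PFS from the start of radiotherapy, experimental arm against the historical arm (Ahist), the primary comparison.
- **Test.** Statistical methods {20a}: "Survival comparisons between groups will be made using the log-rank or Gehan-Wilcoxon test". No rule for choosing is given, and the sentence covers both PFS and OS.
- **Model.** The same section: "The Cox proportional hazards model will be used to calculate the hazard ratio in univariable and multivariable analyses". It names no covariates and does not say whether the primary conclusion rests on this model or on the rank test. It also plans to compare patient characteristics between arms.
- **Adjustment.** Additional analyses {20b} opens by marking the item as not applicable and continues: "The subgroup and adjusted analyses are not planned".
- **Sample size {14}.** The calculation assumes proportional hazards, 5% significance and 80% power, with 65 events to detect a hazard ratio of 1.65 and 67 patients. Ahist has 44 patients and a median PFS of 4.9 months.
- **Sources of difference the protocol names.** The Background {6a} links non-radical resection to a higher risk of early progression and unmethylated MGMT to worse survival. The concomitant-care section {11d} leaves the regimen to the physician and says the shorter one generally goes to frail and elderly patients.

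**The concern.** Without randomisation, nothing in the design balances prognosis between the arms. They come from different calendar periods (2014–2018, and recruitment from October 2020), and the protocol itself identifies characteristics on which they could differ. An unadjusted rank test credits any such difference to PET, or lets it hide a PET effect. The planned table of baseline characteristics would show an imbalance but would not correct for it.

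The analysis text leaves two things open. Sections {20a} and {20b} do not agree on whether an adjusted analysis exists. Section {20a} also permits either of two tests that weight early and late events differently. The historical result is already known and the trial is open-label, so a choice made at analysis would not be blind to outcome. The only primary conclusion is at stake.

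**Working it through.** **Step 1. The plan's own figure.** Freedman's formula at two-sided 5%, 80% power, HR 1.65 and equal arms:

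(1.960 + 0.842)² × [(1 + 1.65)/(1 − 1.65)]² / 2 = 7.849 × 16.62 / 2 = 65.2 events per arm.

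The 65 is therefore reproduced as a per-arm count under proportional hazards, the setting to which the log-rank test belongs. The adjustment question does not depend on this figure.

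**Step 2. The analysis statements side by side.**

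| Question | {20a} | {20b} |
|---|---|---|
| Is an adjusted model planned? | Yes, multivariable Cox | No |
| Does it carry the primary conclusion? | Not stated | – |
| Which test compares PFS? | Either of two, no rule | – |

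If {20b} means only that nothing is added beyond {20a}, the first row is reconciled. The other two rows stay open.

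**Step 3. What a case-mix difference could do.** All imbalance inputs here are assumptions. Take a favourable factor with HR 0.5, present in 50% of trial and 30% of historical patients, and no PET effect. The ratio of average hazards (an approximation) is

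(0.5 × 0.5 + 0.5) / (0.3 × 0.5 + 0.7) = 0.75 / 0.85 = 0.882.

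Two independent factors of this kind give 0.882² = 0.779.

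The standard error of the log hazard ratio is √(1/d + 1/44), with d experimental events and all 44 historical patients counted as events. With uniform accrual over 38 months, 6 months' further follow-up and exponential PFS, 67 patients yield 67 × 0.826 = 55.3 events at a median of 8 months, and 67 × 0.921 = 61.7 at a median of 4.9 months. The probability of a significant result in favour of PET is Φ(|ln HR| / SE − 1.96):

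| d | SE | No imbalance | One factor (0.882) | Two factors (0.779) |
|---|---|---|---|---|
| 55.3 | 0.202 | 2.5% | 9.0% | 23.6% |
| 61.7 | 0.197 | 2.5% | 9.2% | 24.5% |
| 65 | 0.195 | 2.5% | 9.4% | 24.9% |

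The choice of d hardly matters: about 9% and about 24%.

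A 20,000-run simulation (44 against 67 patients, no PET effect) agrees. An adverse factor with HR 2, at 60% in the historical arm and 40% in the trial, gives a false benefit by log-rank in 9.7% of runs. At 65% against 35% it is 16%, and at 70% against 30% it is 25%.

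**Step 4. The other direction.** If the same single factor favours the historical arm, a true HR of 1.65 appears as 1.65 × 0.882 = 1.46. Power at d = 55.3 then falls from 70% to 46%. Nothing in the protocol says which direction applies.

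**Step 5. The open choice of test.** Type I error when there is no imbalance and no PET effect:

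| Simulation | Log-rank | Gehan-Wilcoxon | Smaller p-value of the two |
|---|---|---|---|
| 20,000 runs, two-sided | 5.1% | 4.6% | 7.0% |
| 4,000 runs, two-sided | 5.5% | 5.4% | 7.6% |
| 20,000 runs, favouring PET only | 2.7% | 2.5% | 3.7% |

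The last column is a worst case, because the protocol does not say that the smaller p-value will be reported.

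**The case against.** The strongest reply is that {20a} is the section for primary and secondary outcomes and already contains multivariable Cox models, while {20b} deals only with extras. On that reading, adjustment is in the plan. The covariate list and the final choice of test are also matters for an analysis plan that is not shown. This has force: a reader might infer that the protocol forbids adjustment outright, and the text does not support that. Nor is the absence of a covariate list a fault in itself. What remains is that {20b} says the opposite of {20a} in plain words. Even on the generous reading, the multivariable model has no stated part in the primary conclusion. An analysis plan that makes it primary would have to depart from the wording of {20b}.

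A reader might also infer that the historical patients were less strictly selected, because the trial sets performance-status and laboratory limits and states "biopsy only = exclusion criterion". Or that they had less adjuvant treatment, because the trial's 6-week regimen "can be extended to 12 cycles of adjuvant temozolomide". The protocol supports neither. It describes Ahist in one sentence and does not report its performance status, laboratory values, biopsy status or number of cycles. The one criterion it does give, indication for adjuvant chemoradiotherapy, is also a trial criterion. These points are unknown, not shown to differ.

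It is also fair to say that the prevalences and hazard ratios above come from no section of the protocol. They illustrate sensitivity and do not estimate bias.

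**Conclusion.** The point holds. A comparison declared confirmatory against a non-randomised cohort has contradictory statements on adjustment, no stated role for the adjusted model, and two permitted tests with no rule, although the sample size assumes proportional hazards. As written, the primary PFS conclusion cannot separate a PET effect from case mix.

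The amount and direction of bias cannot be determined from the protocol. Under the assumed imbalances, the chance of a false benefit rises from 2.5% to about 9% with one factor and about 24% with two. The open test choice is the smaller matter: at most about 7 to 7.6% two-sided, against roughly 5%. Adjustment should be settled before analysis because it bears directly on the primary conclusion; naming the test is a wording correction.

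**What to change.** 1. Reconcile {20a} and {20b} by removing only the words in {20b} that exclude adjusted analyses. Keep the statement that no subgroup analyses are planned.
2. Pre-specify one primary adjusted PFS comparison, either a Cox or a propensity-weighted hazard ratio. Fix the covariates in advance, for example age, ECOG status, extent of resection, MGMT status and regimen, limited to those available in both cohorts.
3. Name the log-rank test as the single unadjusted test, in line with the proportional-hazards assumption in the sample size.
4. Check Ahist against the trial's eligibility criteria, report the result, and add a sensitivity analysis restricted to the Ahist patients who meet them.

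**Cost.** Protocol and analysis-plan wording, plus analyst time; the trial already records these covariates. Weighting or restriction loses effective sample size from only 44 historical patients. The protocol does not say which covariates exist for Ahist, so that must be established before the set is fixed. Adjustment also cannot remove differences in unmeasured factors or in calendar period, and the report should say so.

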### Definition of analyses population relating to protocol nonadherence and any statistical methods to handle missing data (multiple imputation) {20c}

Protocol nonadherence will be assessed by the principal investigator case by case. Patients with major protocol deviations will be excluded from the analysis. Missing data are not planned to be imputed. However, in the event of substantial missing data for any parameter, a sensitivity analysis using any method of imputation could also be used.

The data will be analysed for the individual groups below:Full Analysis Set (FAS)All patients who successfully completed recruitment met the inclusion/exclusion criteria.Per Protocol Set (PPS)FAS subgroup with such patients who undergo trial without significant deviations from the protocol.Safety SetIncludes all patients who were administered a medicinal product within the framework of the GlioMET study.

## Methods: monitoring

### Data monitoring {21a}

The on-site monitoring of the study conduct is regularly performed throughout the study period to assess the accuracy and completeness of the data. The study site may be subject to a quality assurance visit. If so, the site will be contacted in advance to organize a monitoring visit. The investigator will ensure direct access to all study documents for quality assurance monitors.

### Interim analyses {21b}

Not applicable. An interim analysis is not planned.

### Harms {22}

Serious adverse events will be reported according to standard rules and standard operating procedures of the coordinating unit. All study participants will be monitored for potential adverse events.

### Auditing {23}

Trial conduct will be audited by the Institutional Projects Evaluation Committee every year during the study. The process of auditing will be independent of the investigator and sponsor.

### Research ethics approval {24}

This protocol and the template informed consent form were reviewed and approved by the Ethical Committee of the Masaryk Memorial Cancer Institute (in September 2020) with respect to the scientific content and compliance with applicable research and human subject regulations. Study protocol was evaluated by institutional Project Steering Committee and institutional Ethics Committee No. 2020/1206/MOU.

### Protocol Amendments {25}

Any new protocol modifications will be sent for review by the ethics committee and a national Drug Agency and will be amended at the clinical trial registry.

### Consent and Assent {26a}

Informed consent will be obtained from all participants prior to enrolment in the study.

A trained study investigator will describe the study to patients or authorized surrogates if applicable. Patients will also receive information sheets. The investigator will discuss the study with patients in the sense of the information provided in the information sheets. The investigator will obtain written informed consent from patients willing to participate in the trial. In the case of patients who are unable to consent because of a medical condition, their ability to participate in the study will be assessed by a medical council consisting of at least one independent physician informed about the study details and one study investigator.

### Confidentiality {27}

All study-related information will be stored securely at the study site. All participant information will be stored in locked file cabinets in areas with limited access. All local databases will be secured with password-protected access systems. Forms, lists, logbooks, appointment books, and any other listings that link participant ID numbers to add identifying information will be stored in a separate locked file in an area with limited access.

### Access to data {29}

The final trial dataset will be accessible to all investigators participating in this study.

### Ancillary and posttrial care {30}

The clinical trial GlioMET is conducted in full accordance with the principles of the Declaration of Helsinki (in the latest valid version), in accordance with GCP requirements and in accordance with applicable national and European legislation. GlioMET was discussed and approved by the local ethics committee and State Institute for Drug Control before the start.

All patients were informed about the possible risks of their participation in this study and about the possibility of ending their participation in the study at any time without consequences. The patients are also informed about the measures that will be taken for the protection of personal data and about the fact that, in the event of damage to health as a result of the implementation of the study, liability insurance for the examiner and the contracting authority has been arranged in accordance with the applicable legislation, through which the possible compensation of assessment subjects.

### Dissemination policy {31a}

We intend to submit the results of the study to be published in a peer-reviewed international medical journal and disseminate them to academic and healthcare professionals via presentations at conferences.

## Data Availability

No datasets were generated or analysed during the current study.

## Abbreviations

2D-ROI: Two-dimensional region of interest
3D-ROI: Three-dimensional volume of interest
^11^C-methionine: 11 Carbon radiolabelled methionine
^18^F-FET: 18 Fluorine radiolabelled fluoroethyltyrosine
^18^F-FLT: 18 Fluorine radiolabelled fluorothymidine
^18^F-DOPA: 18 Fluorine radiolabelled dihydroxyphenylalanine
AA: Aminoacid
ALT: Alanine aminotransferase
AST: Aspartate aminotransferase
ATRX: Alpha-thalassemia X
CHT: Chemotherapy
D: Day
ECOG: Eastern Cooperative Oncology Group
eCRF: Electronic Case Report Form
EORTC: European Organization for Research and Treatment of Cancer
FAS: Full analysis set
FDG: 2-Deoxy-2-[18F] fluoro-D-glucose
FET: Fluoroethyltyrosine
Fri: Friday
GBM: Glioblastoma multiforme
GCP: Good clinical practice
GFAP: Glial fibrillary acidic protein
HBV: Hepatitis B virus
HCV: Hepatitis C virus
HIV: Human immunodeficiency virus
ID: Identificational data
IDH1: Isocitrate dehydrogenase 1
IDH2: Isocitrate dehydrogenase 2
IHC: Immunohistochemistry
IQR: Interquartile range
Ki-67 index: Marker of proliferation Kiel 67
M: Month
MET: Methionine
MEYS: Ministry of education, youth and spo
MGMT: O^6^-methylguanine-DNA methyl-transferase
miRNA: Micro-ribonucleic acid
MMCI: Masaryk Memorial Cancer Institute
Mon: Monday
MR: Magnetic resonance
MRI: Magnetic resonance imaging
OP: Overall survival
PD: Progressive disease
PDL1: Programmed Cell Death Ligand 1
PET/CT: Positron emission tomography/computer tomography
PFS: Progression-free survival
PoF: Patterns of failure
PPS: Per Protocol Set
preRT: Preoparative radiotherapy
PS: Performance status
QLQ: Quality of Life Questionnaire
RANO: Response Assessment in Neuro-Oncology
REP: Rapid early progression
RT: Radiotherapy
SUVavg: Average value of standardized uptake value
SUVmax: Maximum value of standardized uptake value
SD: Standard deviation
T/B ratio: Tumour to background ratio
TERT: Telomerase reverse transcriptase
TMZ: Temozolomide
ULN: Upper limit of normal
WHO: World Health Organization
